## **B. Physical Exercise/Physiotherapy Risks**

- **Musculoskeletal Injuries:** Risks of strains, sprains, especially in those unaccustomed to physical activity (Macera et al., 2003).
- **Cardiovascular Events:** Exercise can trigger events like myocardial infarction in at-risk populations (Thompson et al., 2007).
- **Fatigue and Overexertion:** Inadequate pacing may lead to dizziness or syncope (O'Halloran et al., 2007).

## **C. Psychosocial Support Risks**

- **Emotional Distress:** Discussions may evoke anxiety or depression, especially if participants struggle with conditions (Baikie & Wilhelm, 2005).

- **Non-compliance with Intervention:** Perceived inadequacy may lead to withdrawal (Tong et al., 2012).
- **Dependence on Support Services:** Participants might rely excessively on services, hindering independence (Cumming, 1996).

#### **D. General Risks**

- **Withdrawal from Trial:** Adverse events or perceived ineffectiveness may lead to withdrawal.
- **Infections:** Risk of infections with interventions involving close contact, particularly for immunocompromised individuals (Geraci et al., 2009).
- **Psychological Effects of Monitoring:** Frequent evaluations could cause health anxiety (Clarke et al., 2013).

---

#### **2.3.2 KNOWN POTENTIAL BENEFITS:**

Systematic reviews suggest that interventions targeting frailty and multimorbidity significantly improve quality of life and decrease mortality and morbidity rates. Although most evidence originates from high-income countries, the insights can guide interventions globally, including in India.

##### **i. Improvement in Frailty:**

- Comprehensive interventions can reduce frailty and improve physical function in older adults. Studies show enhanced muscle strength and mobility (Clegg et al., 2013; Puts et al., 2017).

##### **ii. Enhanced Quality of Life:**

- Targeted interventions lead to improved mental and emotional well-being. Frail individuals often experience better life satisfaction and reduced depression (Dent et al., 2016).

##### **iii. Reduction in Morbidity and Mortality:**

- Addressing multimorbidity can decrease hospitalization rates and overall mortality. Integrated care models improve health outcomes by managing chronic conditions effectively (Fried et al., 2001; Adlins et al., 2014).

**iv. Local Relevance:**

- This trial addresses the critical gap in evidence for interventions tailored for older adults in India, contributing valuable data to the field and informing policy development ([name] et al., 2020).

**v. Improved Healthcare Utilization:**

- Coordinated care reduces unnecessary healthcare use and costs, optimizing resource allocation for better overall efficiency (Hoogendijk et al., 2019).

---

### **2.3.3 ASSESSMENT OF POTENTIAL RISKS AND BENEFITS**

The assessment of potential risks and benefits will be an ongoing process throughout the trial to ensure participant safety and the efficacy of the intervention. A multidisciplinary team including clinical trial coordinators, physicians, physiotherapists, dietitians, and social workers will conduct this assessment.

#### **A. Roles and Responsibilities**

**a) Clinical Trial Coordinator/Manager:**

- Oversee the risk/benefit assessment process.
- Ensure adherence to ethical guidelines and regulatory requirements.
- Maintain communication with the Institutional Ethical Committee (IEC) and other regulatory bodies.

**b) Principal Investigator (PI):**

- Lead the overall assessment and make final decisions regarding participant safety.

- Review data from adverse event reports and assess the need for protocol modifications.

**c) Medical Staff (Physicians, Nurses):**

- Conduct initial health screenings and ongoing health assessments of participants.
- Monitor and document any adverse events.

**d) Physiotherapists:**

- Evaluate physical capabilities and risks associated with exercise regimens.
- Monitor participants during physical activities to minimize injury risks.

**e) Dietitians:**

- Assess nutritional needs and risks associated with supplementation.
- Provide education on dietary modifications.

**f) Social Workers:**

- Evaluate psychosocial factors impacting participant adherence and well-being.
- Provide support and resources to address emotional distress related to chronic conditions.

**B. Stages of Assessment**

**i. Pre-Enrollment Stage:**

- a. Conduct comprehensive assessments of each participant's health status, medical history, current medications, and psychosocial factors.
- b. Utilize standardized assessment tools (e.g., frailty index, quality of life scales) to establish baseline data.

ii. **Initial Assessment (During Enrollment):**

- a. Review participant eligibility and identify contraindications for specific intervention components.
- b. Document pre-existing conditions that may increase risk.

iii. **Ongoing Monitoring (Throughout the Trial):**

- a. Regular health check-ups scheduled at 6, and 12 months to track health changes, adherence, and adverse events.
- b. Continuous documentation and reporting of any adverse effects to the PI and trial coordinator.
- c. Continuous overview and monitoring by an independent Drug, Data Safety and Monitoring Board (DSMB)

iv. **Post-Assessment Reviews (After Each Assessment Phase):**

- a. Conduct review meetings involving the multidisciplinary team to evaluate data from health assessments, adverse event reports, and participant feedback.
- b. Discuss trends, potential safety issues, and the effectiveness of the intervention.

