## 4.2 SCIENTIFIC RATIONALE FOR STUDY DESIGN

The use of a cluster randomized design is essential in this trial to effectively evaluate the Multi-FrAME intervention's impact within the urban Primary Healthcare Centres (PHCs) of Bhubaneswar city. Given the nature of the intervention, which includes various components at the healthcare center level, randomizing at the cluster level reduces contamination risks between participants receiving the intervention and those receiving standard care.

This design is particularly relevant in the context of Bhubaneswar's urban PHCs, where healthcare practices can vary significantly. By employing a cluster approach, the trial can assess the intervention in a way that mirrors real-world application, enhancing external validity. Randomization at the PHC level allows for the capture of data reflecting the complex interactions and systemic changes induced by the intervention. This will also improve future possibility of uptake into systems as the intervention is being tested at the point of proposed delivery through the system.

The observer-blinded aspect of the study further strengthens its validity by reducing assessment bias. Blinding ensures that outcome evaluators remain unaware of which group (intervention or control) the participants belong to, thus minimizing potential biases in data collection and interpretation.

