#### 12.4.7 PLANNED INTERIM ANALYSES:

- **Objective:** To assess the safety and efficacy of the Multi-FrAME intervention at an intermediate point, ensuring ongoing participant safety and verifying preliminary effectiveness results.
- **Timing:** The interim analysis will be conducted after 50% of participants have completed the 12-month follow-up.
- **Criteria:**
  - **Safety:** Evaluate the incidence and severity of adverse and serious adverse events.
  - **Efficacy:** Assess primary and secondary outcomes, focusing on health-related quality of life (EQ-5D-5L) and frailty index changes.
- **Statistical Considerations:** The analysis will not impact the overall type I error rate as it's not stopping the trial for efficacy. We will use descriptive statistics to identify any emerging trends or safety concerns.
- **Decision-Making Process:** An independent data monitoring committee (DMC) will review interim results. Recommendations will be made regarding the continuation, modification, or early termination of the trial based on predefined criteria.

- **Reporting:** Findings will be documented and shared with the ethics committee without full disclosure to the research team, unless necessary for participant safety.

---

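### Section 2.3.3 lets a team that includes delivery staff discuss the effectiveness of the intervention after each assessment phase, which does not fit the interim disclosure rule in 12.4.7 or the data-access rule in 13.4

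*Protocol*

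**What the plan says.** Protocol 2.3.3 states who carries out the ongoing risk/benefit assessment: "A multidisciplinary team including clinical trial coordinators, physicians, physiotherapists, dietitians, and social workers will conduct this assessment". The principal investigator leads it and is also to "Review data from adverse event reports and assess the need for protocol modifications".

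Under B, Stages of Assessment, item iv is headed "Post-Assessment Reviews (After Each Assessment Phase"). It has two parts. The team is to "Conduct review meetings involving the multidisciplinary team to evaluate data from health assessments, adverse event reports, and participant feedback", and then to "Discuss trends, potential safety issues, and the effectiveness of the intervention". Item iii of the same list gives the post-baseline schedule: "Regular health check-ups scheduled at 6, and 12 months to track health changes, adherence, and adverse events".

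Three other sections bear on who may see accumulating results:

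- **12.4.7** plans one interim analysis of safety and efficacy, after half the participants have completed 12 months. An independent data monitoring committee reviews it, and findings go to the ethics committee "without full disclosure to the research team, unless necessary for participant safety".
- **13.4** makes the trial database accessible only to the principal investigator and the statisticians.
- **4.2 and 6.4** blind the outcome evaluators ("Blinding ensures that outcome evaluators remain unaware of which group" a participant belongs to), and **12.4.1** blinds the data analysts. No blinding is stated for anyone else.

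**The concern.** Item iv lists effectiveness separately from safety, so the meeting is not a safety review alone. Those attending include people who supervise exercise, give dietary education and provide psychosocial support (2.3.3 A). The package is openly delivered and allocated by health centre, so these people can be expected to know the arm of the centre where they work.

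If they discuss during follow-up whether the package is working, two things can shift before month 12: how hard the package is delivered, and what participants are led to expect. Participants know what care they receive, and the primary outcome is their own report on the EQ-5D-5L. Restricting access to interim efficacy is meant to prevent this, and 12.4.7 does restrict it. Item iv has no matching restriction.

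**Working it through.** No figure in the plan is at stake. The check sets the sections side by side.

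| Question | 2.3.3 B.iv | 12.4.7 | 13.4 |
|---|---|---|---|
| Who looks | Multidisciplinary team, including delivery roles | Independent committee | Principal investigator and statisticians |
| At what | Health-assessment data, adverse events, feedback; effectiveness discussed | Adverse events; primary and secondary outcomes | Trial database |
| When | After each phase, so at month 6 and month 12 | Half of participants past month 12 | Throughout |
| Limit on the team | None stated | Full disclosure withheld except for safety | No access |

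**1. Does the meeting fall before the final primary assessment?** In participant time, yes: month 6 precedes month 12. In calendar time it depends on accrual, which the protocol does not give. Assume uniform accrual over A months, one trial-wide review when the 6-month phase closes, and no drop-out.

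- The review falls at A + 6. The last month-12 visit is at A + 12, so the review always comes first.
- A participant enrolled at time t still awaits month 12 if t + 12 > A + 6, that is t > A − 6. The share waiting is min(1, 6/A): all of them if A is 6 or less, and half if A = 12.
- The interim trigger falls at A/2 + 12. The review precedes it when A + 6 < A/2 + 12, that is when A < 12.

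**2. Does the absence of a formal test remove the conflict?** No. The interim in 12.4.7 is also descriptive and is said not to stop the trial for efficacy, yet the protocol still restricts who sees it. The same reasoning applies to item iv.

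**3. Is there a route by which outcome data could reach the meeting?** Section 13.4 gives the team no database access, but it gives access to the principal investigator, who leads the assessment under 2.3.3. Section 13.4 also says that findings, once reviewed by the steering committee, are shared with the research team, without saying when. Item iv itself has the team evaluate health-assessment data.

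**4. Is alpha spent?** No test or decision boundary is attached to the meetings. Two unadjusted two-sided looks at 0.05 would give a type I error of about 0.091, 0.083 or 0.078 at assumed between-look correlations of 0.5, 0.7 or 0.8. That does not describe what item iv plans.

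**The case against.** The strongest reply is that item iv is a clinical review, loosely worded. It names neither the EQ-5D-5L nor a comparison by arm. The nearest antecedent for its data is the 6- and 12-month health check-up, and quality-of-life and frailty tools appear in that list only for baseline. Delivery staff will form impressions of benefit anyway from monthly contact and diary review.

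Much of this stands, and it limits the point. Four stronger readings that a reader might infer are not supported:

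- **That the team is handed the equivalent of the committee's interim.** The text does not say that results are aggregated or shown by arm. It only fails to prevent it.
- **That the package can be amended in response to observed efficacy.** Section 2.3.3 C ties modifications to significant identified risks and requires ethics approval of amendments, and 13.7 sends any protocol change to the DSMB.
- **That the team conducts the month-12 interviews.** Sections 4.2 and 6.4 assign outcomes to blinded evaluators, and nothing places those evaluators in the meeting. Section 9.1 has the EQ-5D-5L administered by an investigator, which does not mean by the delivery team. Whether the combined monthly sessions in 6.2 strain the blinding is a separate matter.
- **That safety is unsupervised.** Item iii of the same list provides continuous independent DSMB oversight.

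The reply does not explain why effectiveness is listed as a topic in its own right, or why the disclosure rule in 12.4.7 has no counterpart in item iv. That impressions form anyway is no reason to add a scheduled discussion of them.

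**Conclusion.** The concern holds as an inconsistency between sections. Item iv permits a discussion of effectiveness, from month 6, by a team that includes unblinded delivery roles, while 12.4.7 and 13.4 restrict the same kind of information. It is a conduct rule stated in this protocol, not a detail left to a statistical analysis plan. It should be corrected, and it does not by itself invalidate the 12-month comparison.

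The conclusion rests on two inferences. Delivery staff know their centre's allocation, which follows from open delivery by centre with blinding stated only for evaluators and analysts. The team, which includes the trial coordinators, overlaps with the research team of 12.4.7, a term the protocol does not define.

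The size of any bias cannot be derived. The target difference is 0.10 × 0.87 = 0.087. An assumed expectation shift of 0.02 to 0.03 would be 0.02/0.087 = 23% to 0.03/0.087 = 34% of it, but nothing in the document supports that shift, so the percentages only restate the assumption.

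**What to change.** - **2.3.3 B.iv:** remove effectiveness from the topics discussed. State that team meetings consider safety, tolerability and delivery problems in individual participants, or pooled data without arm labels. Pooling should be across centres, because a summary by centre is a summary by arm for anyone who knows the allocation.
- **2.3.3 or 12.4.7:** state that any summary of outcomes or adverse events by arm is prepared by the statistical team and goes only to the DSMB/DMC. Coded arms would keep this consistent with the blinding of analysts in 12.4.1.
- **13.4:** say when findings are shared with the research team, and exclude by-arm results during the trial except under the safety exception already in 12.4.7.

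The cost is a few sentences of protocol text. The team loses an informal look at effectiveness while the trial runs. Review of individual participants' safety, the DSMB's role and the existing rule on modifications stay as they are.

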**C. Actions Following Assessment**

i. **Intervention Adjustments:**

- a. Implement modifications if significant risks are identified (e.g., adjusting dosages, altering exercise regimens).
- b. Protocol amendments submitted to the IEC for approval before implementation.

ii. **Participant Communication:**

- a. Inform participants of any intervention changes, the rationale, and potential impacts on safety and well-being.
  - b. Provide additional education and resources to address identified risks.
- iii. **Emergency Protocols:**
  - a. Develop and communicate protocols for addressing severe adverse events or complications.
  - b. Ensure staff are trained in emergency response procedures to protect participant safety.
- iv. **Final Evaluation and Reporting:**
  - a. Conduct a comprehensive analysis of risks and benefits observed throughout the study.
  - b. Prepare a report for the IEC and stakeholders detailing findings, including management of serious adverse events.

### 3 OBJECTIVES AND ENDPOINTS

The primary healthcare intervention package (Multi-FrAME) is expected to improve health outcomes for older adults with multimorbidity and frailty, including a reduction in frailty progression and enhanced functional ability. This will assess the following outcomes.

| Objectives                                                                                      | Endpoints                                                   | Justification For Endpoints                                                       | Putative Mechanisms Of Action                                   |
|-------------------------------------------------------------------------------------------------|-------------------------------------------------------------|-----------------------------------------------------------------------------------|-----------------------------------------------------------------|
| 3.1 PRIMARY OBJECTIVES                                                                          |                                                             |                                                                                   |                                                                 |
| Assess the effectiveness of the Multi-FrAME package in improving health-related quality of life | Change in EQ-5D-5L index scores at 0, 6, and 12 months      | EQ-5D-5L is validated for use in India and measures multiple dimensions of health | Comprehensive care improves physical, mental, and social health |
| 3.2 SECONDARY OBJECTIVES                                                                        |                                                             |                                                                                   |                                                                 |
| Evaluate improvement in frailty                                                                 | Change in frailty index scores (deficit accumulation model) | Reliable measure for frailty changes                                              | Nutritional support and physical activity reduce frailty        |
| Assess improvement in ADL/IADL                                                                  | Change in ADL/IADL scores using Lawton IADL Scale           | Validated measure for functional status                                           | Improved physical and cognitive functioning                     |
| Decrease healthcare utilization                                                                 | Reduction in healthcare visits and hospital admissions      | Reflects stabilized health conditions                                             | Coordinated care reduces the need for acute services            |
| Decrease healthcare expenditure                                                                 | Reduction in total healthcare costs                         | Economic impact of reduced healthcare spending                                    | Efficient management techniques                                 |

|                               |                                                                |                                            |                                                      |
|-------------------------------|----------------------------------------------------------------|--------------------------------------------|------------------------------------------------------|
| Improve medication adherence  | Increase in Medication Adherence Reporting Scale (MARS) scores | Indicates adherence behavior changes       | Education and psychosocial support improve adherence |
| Increase patient satisfaction | Higher scores in Patient Satisfaction Questionnaires           | Direct feedback on care experience         | Patient-centered care enhances satisfaction          |
| Reduce mortality rates        | Reduction in all-cause mortality over study duration           | Key determinant of long-term effectiveness | Comprehensive care strategies prolong life           |

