| Medical Management                  | Medication review and optimization; Diary for improving adherence and compliance                                                                                         | Monthly, with diary data being updated daily                                                                                                                                                                                 | In-person at PHC                            | Self-care, with caregiver assistance if needed |
| Nutritional Support                 | Vitamin D3, iron, folic acid, calcium, and protein supplements                                                                                                           | Doses are subject to the results of participants' biochemical tests for the respective nutrients. These doses will be monitored and modified as necessary to maintain nutrient levels within the biological reference range. | Oral supplementation                        | Self-care                                      |
| Physiotherapy and Physical Activity | Customized exercise program                                                                                                                                              | Monthly sessions, with daily exercises                                                                                                                                                                                       | In-person sessions and home-based exercises | Self-care, with caregiver support for safety   |
| Psychosocial Support                | Individual and group therapy sessions (Including therapeutic games, storytelling, friendship enrichment program), health promotion through the health diary IEC material | Breathing exercise and Meditation on daily basis, Psychological Counselling as per the patient's requirement, and Group sessions once in 2-3 month                                                                           | In-person or via tele-health                | Self-care                                      |

Details of the intervention are provided as an additional file.

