**B. Secondary Endpoints:**

i. **Frailty Index:**

- a. **Tool:** Cumulative Deficit Frailty Index (Rockwood et al., 2005)
- b. **Details of the index:** The study will employ a deficit-based frailty index (FI) to assess frailty status, following the cumulative deficit model (Ghosh et al., 2023). The FI will be constructed using 40 health-related variables covering multiple domains, including chronic diseases, functional limitations, cognitive impairments, and self-perceived health status. Each variable will be coded as 0 (deficit absent), 1 (deficit present), or assigned an intermediate value (e.g., 0.5) for partial deficits. The FI score for each participant will be calculated by dividing the total number of deficits present by the total number of variables assessed, resulting in a score ranging from 0 to 1. Based on this score, participants will be categorized as robust ( $FI \leq 0.15$ ), prefrail ( $FI > 0.15$  to  $\leq 0.24$ ), or frail ( $FI > 0.25$ ). This method provides a comprehensive and standardized approach to measuring frailty by accounting for the accumulation of health deficits across multiple domains.
- c. **Assessment Schedule:** Assessed at baseline, 6, and 12 months.

ii. **ADL/IADL:**

- a. **Tool:** Lawton and Brody Instrumental Activities of Daily Living Scale (Lawton & Brody, 1969)
- b. **Assessment Schedule:** Conducted at baseline, 6, and 12 months.

iii. **Healthcare Utilization:**

- a. **Tool:** Custom questionnaire capturing healthcare visits and hospital admissions.
  - b. **Data Collection:** Monthly via participant health diaries and healthcare records.
- iv. **Healthcare Expenditure:**
  - a. **Assessment:** Monthly data collection from participant reports and receipt submissions.
- v. **Medication Adherence:**
  - a. **Tool:** Medication Adherence Reporting Scale (MARS) (Thompson et al., 2000)
  - b. **Frequency:** Assessed at 0, 6, and 12 months.
- vi. **Patient Satisfaction:**
  - a. **Tool:** Patient Satisfaction Questionnaire (Greenfield & Attkisson, 1989)
  - b. **Frequency:** Evaluated at 6, and 12 months.
- vii. **Mortality Rates:**
  - a. **Data Collection:** Continuous monitoring throughout the study period using health records and family reports.

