#### 12.4.3 ANALYSIS OF THE SECONDARY ENDPOINT(S)

- **Outcomes:** Frailty progression, ADL/IADL scores, healthcare utilization, costs, patient satisfaction, medication adherence, mortality, along with all the laboratory measurements.
- **Method:** Each secondary outcome will be clearly defined and analyzed to evaluate the broader impacts of the intervention on participants' health and well-being. Frailty progression will be assessed through a frailty score as a continuous measure. Functional limitations will include work-limiting conditions, mobility, Activities of Daily Living (ADL), and Instrumental Activities of Daily Living (IADL), scored on an ordinal scale, using categorical measures (e.g., "able" vs. "unable"). Health care utilization will be measured by tracking healthcare events (e.g., visits, hospitalizations) in a binary or categorical format, while health care expenditure will be recorded as a continuous variable, capturing both mean and median expenditures. Medical adherence will be represented as a percentage, indicating the proportion of prescribed medications participants adhered to. Statistical comparisons of these secondary outcomes between the intervention and control groups will employ appropriate tests for each outcome variable type to assess differences. Mixed-effect models will calculate adjusted odds ratios to determine effect sizes, with corresponding confidence intervals to quantify the intervention's impact.

---

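### The total-cost endpoint is measured only through participant spending, and the utilisation endpoint does not exclude the package's own monthly PHC sessions

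*Protocol*

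**What the plan says.** **Cost.** The objectives and endpoints table (Protocol section 3.2) sets an objective of lower healthcare expenditure and defines its endpoint as "Reduction in total healthcare costs". Section 9.1, B.iv, names one way of collecting it: "Monthly data collection from participant reports and receipt submissions". Section 12.4.3 includes costs in its list of outcomes and treats expenditure as a continuous variable. No section states a costing perspective or collects the cost of providing the package.

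**Utilisation.** The same table defines this endpoint as "Reduction in healthcare visits and hospital admissions". The mechanism it gives is narrower: "Coordinated care reduces the need for acute services". Section 9.1, B.iii, gives the tool as a "Custom questionnaire capturing healthcare visits and hospital admissions", with data gathered "Monthly via participant health diaries and healthcare records". Section 12.4.3 says: "Health care utilization will be measured by tracking healthcare events (e.g., visits, hospitalizations) in a binary or categorical format".

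**The package.** Section 6.2 has PHC professionals deliver it at the centres, with the study team assisting. Medical management is in person at the PHC, at a frequency of "Monthly, with diary data being updated daily". The monthly sessions combine data collection with clinical management and physiotherapy. Section 6.3 says delivery relies on the centres' own facilities and resources. The comparator is routine care.

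**The concern.** Both problems concern what is counted.

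On cost, the label promises the whole bill while the source covers the participant's share. The package includes medication review, physiotherapy, counselling and supplements. Where the PHC supplies something a participant would otherwise have bought, receipts fall although the resource is still used. This matters because the Protocol looks beyond the household. It hopes to inform policy (2.1), expects coordinated care to cut unnecessary use and cost (2.3.2) and stresses scalability (4.3). Receipts cannot carry conclusions at that level.

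On utilisation, the intervention is itself a series of healthcare contacts. The endpoint takes in visits without restriction, and one of its sources is healthcare records, where clinical contacts at a PHC would be expected to appear. Read literally, the definition takes in the package's own sessions, and no section removes them. The objective is a reduction, so counted sessions work against the package if only its arm attends.

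**Working it through.** The Protocol states no figure for utilisation or cost, so there is nothing to reproduce. The cost half is a comparison of definitions. The utilisation half is illustrative arithmetic on stated assumptions.

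**1. Cost: definition against source**

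Change in total cost = change in participant spending + change in provider and package cost.

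- Section 9.1, B.iv, observes the first term only.
- The second term includes PHC staff time and facility use (6.2, 6.3). No section collects it.
- If participant spending falls by x and delivering the package costs y per participant, the recorded change is −x and the total change is −x + y. The recorded figure overstates any total saving by y, and has the wrong sign when y exceeds x.
- The documents give no unit costs, so y cannot be computed.

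**2. Utilisation: sessions attended by the intervention arm only, and counted**

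Inputs:
- s = package sessions attended per year. Monthly contact over 12 months gives 12 × 1 = 12 (section 6.2). A lower value of 6 is assumed, to allow for missed sessions and dropout.
- c = control-arm visits per year, assumed 4 to 24.
- r = true relative reduction in non-package visits, assumed 10% to 50%.

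Counted visits in the intervention arm = c(1 − r) + s. Counted difference = s − c·r. True difference = −c·r.

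| c | r | True difference | Counted, s = 12 | Counted, s = 6 |
|---|---|---|---|---|
| 4 | 10% | −0.4 | +11.6 | +5.6 |
| 6 | 25% | −1.5 | +10.5 | +4.5 |
| 12 | 25% | −3.0 | +9.0 | +3.0 |
| 24 | 25% | −6.0 | +6.0 | 0.0 |
| 24 | 50% | −12.0 | 0.0 | −6.0 |

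The counted difference shows a reduction only when c exceeds s/r. For r = 25% this is 12/0.25 = 48 control visits a year at s = 12, or 6/0.25 = 24 at s = 6. Within the assumed ranges, no reduction shows at s = 12.

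**3. Utilisation: both arms attend equally, and sessions are counted**

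The absolute difference stays at −c·r. The relative difference becomes −c·r/(c + s). With c = 6, r = 25% and s = 12, this is −1.5/18 = −8.3%, against a true −25%. With c = 12 it is −3/24 = −12.5%.

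**4. Which arm attends?**

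Section 6.2 places the monthly sessions under the intervention. Sections 1.2, 9.2 and 10.4 describe monthly contact without naming an arm. Either reading is possible, and counting the sessions distorts something under each.

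**5. Scale of analysis**

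The binary or categorical format in 12.4.3 does not fix one pooled any-visit indicator. If such an indicator were chosen and sessions counted, one attended session would make a participant an event.

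**6. What is untouched**

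Package sessions are not admissions, so hospital admissions remain comparable between arms.

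**The case against.** The strongest reply on utilisation is that the Protocol is silent rather than wrong. It never says that package sessions are counted. The rule may sit in the custom questionnaire, the other data collection forms, the manual of operating procedures or the SAP, none of which is shown. This stands in part. A reader might infer that the sessions are definitely counted and have no counterpart in the control arm; the text supports neither statement. What remains is that the endpoint as worded takes the sessions in and nothing shown takes them out. An SAP could add a counting rule, but it could not recover visit types that were never recorded.

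On cost, the objective, the synopsis and section 9.1 all speak of expenditure, which receipts suit well. That too has force: the problem is largely one wide label in the endpoint column. But that cell is the endpoint definition, section 12.4.3 also lists costs, and no collection form or rule could turn a participant-only source into a total cost. The Protocol does not say who pays for supplements, so it should not be assumed that they never generate a receipt. PHC staff time is missed either way.

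Three further inferences go beyond the text:
- That neither objective can be answered. Admissions can be compared, and so can participant spending if named as such.
- That the intervention arm reaches 100% on a binary outcome by construction. Section 12.4.3 leaves room for frequency categories and for admissions analysed alone.
- That excluding the sessions would tilt the result towards the package, because monthly reviews replace ordinary visits. No section says so, and displacement of other visits is arguably part of the effect sought. Restricting the endpoint to acute visits would therefore be a debatable narrowing.

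**Conclusion.** The cost point holds. As defined and collected, the endpoint measures participant spending, and a claim of lower total healthcare cost would be unsupported. Its size cannot be given without unit costs.

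The utilisation point holds as an omission. If only the intervention arm attends and sessions are counted, up to about 12 visits per participant-year are added. Across the assumed 4 to 24 control visits and 10% to 50% true reductions, the counted difference at 12 sessions is +11.6 to 0.0, against a true −0.4 to −12. If both arms attend equally, only the relative effect suffers. The figures rest on assumed visit rates, reductions and attendance, and on the sessions being counted, which the documents leave open.

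Both are secondary endpoints. The conclusion on the EQ-5D-5L primary endpoint is not affected.

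**What to change.** Amend sections 3.2, 9.1 and 12.4.3:

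1. Rename the cost endpoint *participant (out-of-pocket) healthcare expenditure*. Allow a total-cost claim only if package delivery cost is added to the intervention arm, taken as the deliveries recorded on the fidelity form (listed in section 15) multiplied by stated unit costs.
2. Exclude protocol-scheduled contacts from the utilisation endpoint in both arms and report them separately. If the existing questionnaire has no visit-type field, add one.
3. Analyse hospital admissions separately from other visits, each as a count or rate rather than one pooled any-visit indicator.

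The cost is a narrower expenditure claim and one extra data field, with no added participants or visits. Unit costs are needed only if the sponsor wants to keep the total-cost claim.
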